### Secondary outcomes

#### Incidence of adverse events (IAE)

The IAE will include every adverse event during the treatment, unless it is confirmed otherwise. Possible adverse events include infection and exacerbation of lymphedema. Participants will be asked to report any significant changes to their health state following treatment. Once adverse event occurs, it should be closely monitored and meticulously recorded until stabilization or resolution, and the chief designer and the coordinators in charge will be informed immediately. Together with the acupuncturist in charge, they will consult on the case, take proper actions and evaluate the severity. Unless it has been confirmed irrelevant with the intervention of this trial, every possible case should be reported timely to the Institutional Review Board. The chief designer is responsible for the report of all adverse events. The DSMB will inspect periodically to ensure that all adverse events are handled properly.

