### Real acupuncture group

Patients in the real acupuncture group will receive true acupuncture 3 times a week for 4 weeks (12 sessions) at 6 acupoints in each arm: Jianyu (LI 15), Jianliao (SJ 14), Binao (LI 14), Quchi (LI 11), Shousanli (LI 10), and Waiguan (SJ 5). These acupuncture points were selected on the basis of classic TCM record, the published literature [30–35], and the consensus between our experienced acupuncturists. Acupoints are detailed in Fig. 1. After the application of alcohol swabs, these acupoints will be covered by adhesive plaster with plastic rings, and stimulated by manual rotation of the needles accompanied by lifting and thrusting gently to make patients get de qi, which is a sensation of aching or distension or numbness elicited by acupoint stimulation [36, 37]. Then needles will stay put for 30 min.

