### Sham-acupuncture group

Patients in the sham-acupuncture group will receive the same sessions of treatment using Streitberger needles at the same acupoints. Streitberger needles have the appearance of the real needles, however, they will not penetrate the skin. They can be placed at the same acupoints as the real acupuncture group, and held in position by adhesive plaster with a plastic ring, which is conducive to the blinding purpose [38]. When the needle is pushed against the skin, a pricking sensation just like the real insertion will be generated. However, as the pressure increases, the needle shaft will bounce back into the handle, which guarantees the skin unbroken and makes an artificial impression of needle insertion (Fig. 2). Other procedures will be the same with the real acupuncture group, including the application of adhesive plaster and plastic rings.

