### Patient health monitoring

For each participant in both groups, blood pressure and pulse rate will be monitored following every treatment session, whereas routine blood test, ECG test, renal function test and liver function test will be conducted every 2 weeks (Table 1). These data will be monitored closely by DSMB during the trial.

Moreover, as cuts and other breakage of the skin would incur infection and the deterioration of lymphedema, all participants will be warned. For those developing sudden onset of infection, the treatment should be discontinued till the patients have fully recovered and the coordinator in charge should be contacted as soon as possible. In other cases like serious complications and occurrence of other emergencies, where patients are unfit for further therapies, they will be persuaded to quit.

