### Data collection

Before the first treatment session, every participant will get an assessment of both limbs by perometer, which is an automated infrared light digital scanner equipped with a microcomputer. When the limb is placed inside, the infrared light transmitters located on two sides of the perometer will be activated, and the blockage of the transmission of infrared light from both sides caused by the limb will be recorded and calculated. As the transmitters move along the limb, a series of images will be recorded. Hence a highly accurate measurement of the limb size and volume will be created. And these results will serve as the baseline data. Following the treatment of each session, participants in both groups will be asked to take assessments to get the interim data. Upon the last session, the assessments of both limbs will be adopted as the end-point data. For each arm, the measurement will repeat 3 times to ensure the reliability. Table 1 illustrates all the time points when measurements are taken during the whole procedure.

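### The adverse event outcome has no clear end date: as worded, infections or lymphedema exacerbations that start after the last session fall outside it

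*Protocol article*

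**What the plan says.** In the protocol article, the section on incidence of adverse events (IAE) gives the counting rule: "The IAE will include every adverse event during the treatment, unless it is confirmed otherwise". It then names the events expected: "Possible adverse events include infection and exacerbation of lymphedema". Next comes the reporting instruction: "Participants will be asked to report any significant changes to their health state following treatment". For an event that has occurred, it says that "it should be closely monitored and meticulously recorded until stabilization or resolution".

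The section on the real acupuncture group defines treatment as follows: "Patients in the real acupuncture group will receive true acupuncture 3 times a week for 4 weeks (12 sessions) at 6 acupoints in each arm". The sham group follows the same schedule. Under Data collection, the last session closes the limb measurements: "Upon the last session, the assessments of both limbs will be adopted as the end-point data". The Methods part of the abstract says that both primary and secondary outcomes are calculated from data at baseline and at the last session; the IAE is a secondary outcome.

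Two further statements bear on the groups. Patient health monitoring says that "as cuts and other breakage of the skin would incur infection and the deterioration of lymphedema, all participants will be warned". Sham-acupuncture group says that "Streitberger needles have the appearance of the real needles, however, they will not penetrate the skin".

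**The concern.** Evaluating safety is a stated aim of the trial. The protocol itself links broken skin to infection and worsening lymphedema, and these are the two adverse events it names. Neither need be visible on the day of the puncture. If the count stops with treatment, the punctures of the twelfth session get almost no observation time and those of the final week get only a few days.

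Only one group is punctured. Late puncture-related events are therefore lost from the real acupuncture group alone, which shrinks the absolute difference between the groups on the harms that the comparison should detect.

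The paragraph also gives staff two signals: count during treatment, but ask for reports after it. Three centers could apply these differently.

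**Working it through.** The protocol gives no adverse event rate, no time to onset and no planned figure for this outcome, so there is no stated number to reproduce. The check has two parts.

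**The wording, side by side**

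- *Counting rule:* limited to the treatment period. The closing qualifier is unclear. It reads most naturally as an exclusion of some events, and nothing in it extends the time.
- *Reporting instruction:* it refers to the time following treatment. This could mean after each session or after the whole course. It gives no end date and no contact, and does not say that events reported late enter the count.
- *Follow-up to resolution:* this applies once an event has occurred. It tracks known events and does not search for new ones.
- *Source of outcome data:* the abstract and Data collection both end at the last session.
- *Withdrawals:* Loss to follow-up and data management describes a call from the acupuncturist and, where possible, an immediate lymphedema evaluation. It describes no later contact. The sample size section assumes 20% loss, which is 0.20 × 200 = 40 participants.

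So the window is ambiguous, and its most literal reading excludes events that start after session 12.

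**Illustration of size**

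Inputs from the protocol: 12 sessions, 3 a week for 4 weeks, 6 points in each of two arms. Real needling therefore makes 6 × 12 = 72 punctures per arm, or 144 in all. Of these, 6 × 2 = 12 fall in the last session and 3 × 12 = 36 in the last week. Sham makes none.

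Assumptions, none of them in the protocol:

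- sessions on days d = 0, 2, 4, 7, 9, 11, 14, 16, 18, 21, 23, 25;
- equal risk at each session;
- onset uniform over the L days after the responsible session;
- window closing on day 25.

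Share of onsets after the window = (1/12) × Σ max(0, L − (25 − d)) / L.

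| L (days) | Sessions contributing | Sum | Share |
|---|---|---|---|
| 3 | days 23, 25 | (1 + 3)/3 = 1.333 | 1.333/12 = 11% |
| 7 | days 21, 23, 25 | (3 + 5 + 7)/7 = 2.143 | 2.143/12 = 18% |
| 14 | days 14, 16, 18, 21, 23, 25 | (3 + 5 + 7 + 10 + 12 + 14)/14 = 3.643 | 3.643/12 = 30% |

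If the window closes one day later, on day 26, the shares are 6%, 14% and 27%. The result depends on the lag: at L = 28 it is 55%. At the shorter lags, most events are still captured.

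**The case against.** **The window may not be closed.** The reporting sentence may extend past the course, and Table 1, which holds the schedule, is not shown. A condensed article may also leave a numeric cut-off to the full protocol. This stands in part. A reader might infer that events are fixed to count only during the four weeks, but the text supports no more than an ambiguity whose literal reading is narrow. It is still a stated rule that conflicts with the sentence on reporting, not merely a missing detail.

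**Participants may still be seen.** Decongestive therapy includes daily manual lymph drainage at the hospital, recorded by a massage therapist (Table 2), and nothing says that it stops at session 12. This stands too. It cannot be said that late events would go unseen, only that no described step brings them into the IAE.

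**The loss may not be one-sided.** A reader might infer that missed events belong mainly to the real acupuncture group. The protocol supports this only for puncture-related events. Exacerbation can have other causes, both groups receive the same decongestive therapy, all participants are warned about skin breakage, and no rates by group are given.

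**A longer window can dilute a ratio.** Let b be the daily background rate in both groups, p the puncture-related excess per participant and s the share lost. The on-treatment rate ratio is 1 + p(1 − s)/(25b). If a 14-day or 28-day extension captures all the excess, the pooled ratio is 1 + p/(39b) or 1 + p/(53b). With s between 0.11 and 0.30, (1 − s)/25 is 0.036 to 0.028, against 1/39 = 0.026 and 1/53 = 0.019. The pooled ratio thus moves toward 1 even though the absolute excess rises from p(1 − s) to p. The arithmetic is right. It means that a general claim of bias toward no difference depends on the measure, and that the two periods should be reported separately. It does not justify leaving late events uncounted.

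**Conclusion.** The point holds in a limited form. The IAE paragraph contains two phrases about timing that do not agree, and it fixes no end date. Followed literally, infections or exacerbations that begin after the last session are outside the outcome. For puncture-related events, that loss can fall only on the real acupuncture group; for other events it may fall on both.

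The figure of about 11% to 30% is an illustration for onset spread uniformly over 3 to 14 days, under the assumed calendar and equal risk per session. It is not an estimate from the trial's own data, and the between-group effect cannot be calculated. The documents do not support the stronger readings: that all late events are certain to be missed, that the loss is mainly in one group whatever the cause, or that its size is known.

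The primary outcome and the sample size are not affected. This is a cheap improvement to the safety outcome.

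**What to change.** Reconcile the two phrases in the IAE section and define one window: from the first session to a fixed date after the last session attended. It should be identical in both groups and apply to participants who withdraw. The sponsor should choose the length from the longest onset time it considers plausible and state it; under the model above, a window extended by L days captures every onset within L days of a session.

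At the end of the window, existing center staff make one scripted call asking about infection and increased swelling. The caller should be unaware of allocation where feasible. A dedicated blinded nurse need not be required: the Blinding section covers only participants and statisticians, and nurses record first-hand data together with the acupuncturist.

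Report on-treatment and post-treatment events separately by group.

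Cost: a change of wording, about 200 short calls (one per participant), and a closing date for each participant that is later by the length of the added window.

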### Eligibility criteria

In this trial, following inclusion criteria will be adopted:▪ women who have completed breast cancer treatment for more than 1 year;▪ no evidence of recurrence;▪ unilateral lymphedema resulting from surgery for breast cancer;▪ age between 20 and 45;▪ BMI between 18 and 25;▪ mild to moderate lymphedema (10% to 40% increase in volume compared to the unaffected arm).Patients will be excluded as follows:▪ bilateral lymphedema;▪ current use of chemotherapy or radiotherapy;▪ history of bilateral axillary lymph node dissection;▪ serious lymphedema, >40% increase in volume compared to the unaffected arm;▪ pregnant women or overweight women;▪ unable to adhere to the protocol or the treatment schedule;▪ recurrent breast cancer or evidence of other active cancer;▪ current use of diuretics like Diosmin, or other investigational drugs;▪ contraindications for acupuncture, such as infections, open wounds, or broken skin.

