### Sample size calculation

As no two-arm, randomized, multi-centered, sham-controlled trial has been performed on this topic, no existing data regarding the sample size are available. However, based on our preliminary clinical data collected and a similar study [41], we assume that the mean and SD of ARLVR in the real-acupuncture group and sham-acupuncture group are (0.32, 0.25) and (0.22, 0.2), respectively, and after calculation using G-Power (V.3.1), the effect size (ES) is 0.4417261. Next we input the parameters above, set the alpha risk (α, type 1 error risk) and beta risk (β, type II error risk) at 0.05 and 0.2 respectively, and choose “t test from two independent groups” and “A Priori: Compute required sample size given α, power and effect size”, then after calculating, the required sample size is 164 (Additional file 2). Assuming the loss to follow-up rate is 20%, then 197 is the total minimum sample size required in this trial. However, to increase the power and make full preparation, we decided to recruit 200 participants, 100 for each arm in this trial.

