### Statistical and data analysis

Upon the receipt of the final data, the Kolmogorov-Smirnov test (K-S test) will be performed, followed by a test for homogeneity of variance to see whether the variances are equal between groups. If the data distribution fits a normal distribution with equal variance, the independent t test will be employed; otherwise, nonparametric test will be chosen to determine whether there is significant difference between the real acupuncture group and the sham acupuncture group. Moreover, one-way ANOVA will be performed to see whether there is significant difference between three centers. Analysis of covariance adjusted for clinical center and baseline will be applied on the condition that significant difference exists between three centers. In addition, regression analysis will be performed to analyze the effects of co-variances (risk factors) such as BMI, axillary lymph node dissection, postoperative radiotherapy, infection, and history of lymphangitis on the overall outcome of this treatment. A type I level error < 0.05 will be interpreted as statistically significant and 95% CI, mean, and SD will be calculated. Data analysis in this trial will consist of an intent-to-treat (ITT) analysis, a per-protocol (PP) analysis and an interim analysis. The ITT analysis will collect data from all the participants in this trial, and for those loss to follow-up, the last observation carried forward method will be implemented. As for the PP analysis, data collection will be rigorous, and only those participants who strictly comply with the protocol are eligible. The interim analysis in this trial performed by DSMB, will use the interim data collected during the trial to actively monitor the operating status of the trial and help find problems timely. All statistical analyses will be conducted using the SPSS software (version 12).

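### Exacerbation of lymphedema is a named adverse event, but the only case finding described is participants' own report; arm volumes measured at every session are not linked to the count, so measured worsening can go uncounted.

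*Protocol article*

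**What the plan says.** **Harms.** The protocol article, Incidence of adverse events (IAE), gives the scope: "The IAE will include every adverse event during the treatment, unless it is confirmed otherwise". It then names two harms: "Possible adverse events include infection and exacerbation of lymphedema". The case-finding step it describes is "Participants will be asked to report any significant changes to their health state following treatment". No volume criterion is given and the perometer is not mentioned. Severity is evaluated by the chief designer and the coordinators together with the treating acupuncturist. The Blinding section says that acupuncturists know the allocation, while participants and statisticians do not.

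**Arm volumes.** Under Data collection, both limbs are measured by perometer at baseline, with three repeats per arm. The section continues: "Following the treatment of each session, participants in both groups will be asked to take assessments to get the interim data". The last-session readings are the end-point data.

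**Use of the volumes.** The abstract (Methods/Design) reserves baseline and last-session data for the primary and secondary outcomes and gives the rest to interim analyses and monitoring. Statistical and data analysis says that the DSMB's interim analysis "will use the interim data collected during the trial to actively monitor the operating status of the trial and help find problems timely". Neither place connects the readings to the adverse-event count.

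**The concern.** One of the two named harms is a change in the quantity that the trial measures most carefully. The Discussion praises the perometer for its reliability, yet the described route to a safety entry is a participant judging that her health has changed significantly and saying so. A patient whose excess volume rises across sessions, but who does not complain, may have no adverse event recorded. A patient who complains without any rise may have one.

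The limitations paragraph of the Discussion accepts that some sham participants may feel the difference. A count that rests on reporting is therefore open to influence from suspected allocation, and the severity rating involves someone who knows the allocation. The safety table could show few exacerbations, or a distorted difference between groups, while the primary-outcome data contain patients who got worse.

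**Working it through.** **Inputs.** Sample size calculation assumes that the mean and SD of ARLVR in the "real-acupuncture group and sham-acupuncture group are (0.32, 0.25) and (0.22, 0.2), respectively", with 100 patients per arm and 20% loss to follow-up. In words, the Primary outcome section defines ARLVR as the reduction divided by the baseline excess volume, so a value below 0 means that the excess grew.

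**The plan's own figure first.** Pooled SD = √((0.25² + 0.20²)/2) = 0.2264. Effect size = (0.32 − 0.22)/0.2264 = 0.4417, as stated. A two-sided two-sample t test at α = 0.05 and 80% power needs 82 per arm, or 164, as stated (power 0.803). The planning inputs are therefore read correctly. The article gives no expected number of patients who worsen.

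**Illustration.** Assume that ARLVR is normal. The probability that the excess grows by more than a fraction k of its baseline value is Φ((−k − mean)/SD). The expected count is 100 times the sum over the two arms.

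| Net rise in excess at last session | Real | Sham | Expected of 200 |
|---|---|---|---|
| Any (k = 0) | Φ(−1.28) = 0.100 | Φ(−1.10) = 0.136 | 23.6 |
| Above 5% of baseline excess | Φ(−1.48) = 0.069 | Φ(−1.35) = 0.089 | 15.8 |
| Above 10% | Φ(−1.68) = 0.046 | Φ(−1.60) = 0.055 | 10.1 |
| Above 20% | Φ(−2.08) = 0.019 | Φ(−2.10) = 0.018 | 3.7 |

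**Sensitivity of the first row.**
- 20% loss (80 per arm): 80 × (0.1003 + 0.1357) = 18.9.
- Same means and SDs, Pearson III shape: skew +1 gives 100 × (0.058 + 0.109) = about 17; skew −1 gives 100 × (0.108 + 0.134) = about 24.
- Uniform distribution: 100 × (0.130 + 0.182) = about 31.
- A strictly positive distribution: 0.

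**Dependence on the definition.** The printed ARLVR formula has the change in the affected arm as its denominator, not the baseline excess. If the affected arm grows by 50 mL and the other arm is unchanged, it gives (−50 − 0)/(−50) = +100%. Under the printed formula a negative value does not mean worsening, so the table holds only for the definition in words.

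**The case against.** **Self-report is not called exclusive.** The IAE section covers every adverse event during treatment, and participant report is simply the one route it goes on to describe. A reader might infer that a silent patient with rising volume has no adverse event by rule. The text does not say so. This stands: under-counting is a risk, not a certainty.

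**Others see the patients and the data.** Participants attend three times a week, have daily hospital lymph drainage, and the DSMB reviews interim data and inspects adverse-event handling. Deterioration may well be noticed. But noticing is not counting: no stated step turns a reading into an IAE entry.

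**The article condenses a fuller protocol.** An operational definition could sit there, and a missing threshold alone would not be a finding. Here, however, the article states both a capture route for a named harm and a destination for the session volumes, and the two do not meet.

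**The numbers.** A reader might infer that the planning figures imply 24 worsening patients. They do not. Normality is an added assumption: the analysis section plans to test it and has a nonparametric fallback. The 24 also needs the definition in words and full follow-up, and it counts any rise, including measurement noise.

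**Direction.** A reader might infer that incidence will be too low. Complaints without a volume rise push the other way, so the net direction is not established.

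**The 40% limit.** A reader might treat "serious lymphedema, >40% increase in volume compared to the unaffected arm" as a safety threshold during treatment. It is an exclusion criterion at entry, and the document gives it no other role.

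**Conclusion.** The point holds in limited form. For a named harm inside a secondary outcome, the article describes only participant report, has severity evaluated with the unblinded acupuncturist, and leaves unlinked an objective measure already taken at every session. Measured worsening can go uncounted, and the count depends on reporting that the article itself allows may be affected by unmasking. The direction of the error is unknown.

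The size can only be illustrated: about 24 of 200 with any net rise, about 10 above 10% of baseline excess and about 4 above 20%. This rests on normal ARLVR, the definition in words and all 200 measured; with 20% loss the 24 becomes about 19. These are last-session figures and say nothing about transient worsening. The missing link itself does not depend on any of these numbers.

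**What to change.** In Incidence of adverse events (IAE), add a volume-based definition of exacerbation derived from the existing perometer readings:

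- a rise over baseline in affected-minus-unaffected volume beyond a pre-specified margin, confirmed at the next session or at the end point;
- the margin set by the trial team from its own triplicate measurement error. The day-to-day variability in the Discussion, around 0.5, has no unit and cannot serve;
- derivation by the blinded statistician, identically in both groups;
- volume-defined and participant-reported exacerbations tabulated separately.

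Keep the participant report and the immediate notification route as they are; the derived count supplements them and does not replace timely reporting. State also that the session volumes feed this outcome, so that the abstract and the analysis section agree with it.

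The cost is a few sentences and a short derivation, with no new measurement. The downside is that reported adverse-event incidence may be higher in both groups. The derived count removes the dependence on participants' reporting, but not any influence at the measurement itself: the article does not say who operates the perometer, and has first-hand data recorded by the nurse and the acupuncturist.
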